## Introduction

Malnutrition underlies almost half of all childhood deaths in developing countries.^1^ Severe acute malnutrition (SAM) is defined by a weight-for-height Z-score (WHZ) <–3, mid-upper arm circumference (MUAC) <115 mm and/or bilateral pitting oedema.^2^ Current treatment guidelines distinguish two groups: (i) children with uncomplicated SAM who can be managed in the community and (ii) children with complicated SAM, who are hospitalised and undergo resuscitation, stabilisation and nutritional rehabilitation. In-hospital mortality in children with complicated SAM remains high despite the implementation of WHO guidelines.^3^ Furthermore, SAM presents as two major clinical phenotypes: non-oedematous SAM (marasmus), characterised by severe wasting, and oedematous SAM (kwashiorkor), a more complex syndrome characterised by bilateral pitting oedema, steatosis and diarrhoea.^4 5^ Despite differing clinical outcomes, treatment protocols are the same for both oedematous and non-oedematous SAM.

A contributory factor to high inpatient mortality is the co-occurrence of HIV infection in around one-third of children hospitalised for SAM in sub-Saharan Africa.^6 7^ While new HIV infections in children have declined,^8^ a substantial number of infected children are diagnosed late and present with malnutrition. There is also a growing population of HIV-exposed uninfected (HEU) children who have immune abnormalities, poor growth and higher risk of mortality and infectious morbidity.^9^ Hence, HIV has transformed the epidemiology and outcomes of SAM.^10^ Even with standardised treatment approaches, inpatient deaths are almost fourfold higher among HIV-positive children with SAM (herein termed HIV-SAM) compared with HIV-negative children with SAM (30.4% vs 8.4%), for reasons that remain unclear^10^; this mortality is threefold higher than would be expected from anthropometric parameters alone.^10^ Management of HIV-SAM is particularly challenging because HIV fundamentally alters the clinical presentation of malnutrition and the response to treatment. Children with HIV-SAM are more stunted and wasted; have a higher frequency of persistent diarrhoea; tend to have delayed nutritional recovery and have a more complicated clinical course than HIV-negative children with SAM.^10^

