## Sample sizes

### Observational study

The observational cohort will recruit as many children with SAM as possible during the period of enrolment (July 2016 to March 2018), estimated at 600–800 children (capped at 800 maximum), to assess clinical and nutritional outcomes among HIV-positive and HIV-negative children hospitalised with SAM. Assuming mortality of 15%, overall loss to follow-up of 15% and recruitment target of 800 children, there would be 560 evaluable children at 48 weeks, of whom 224 would have HIV-SAM based on an estimated inpatient HIV prevalence of 40%. This will provide >80% power to detect absolute differences of 17% in binary outcomes between HIV-SAM and HIV-negative children with SAM, and of 0.33 times the SD in continuous outcomes.

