## Study outcomes and risk factors

The main study outcomes are clinical (mortality, morbidity and relapse of malnutrition) and nutritional (weight, height, MUAC, leg length, head circumference, mid-thigh circumference, skin-fold thickness and body composition by bioimpedance vector analysis) assessed over 48 weeks of follow-up. Mortality is assessed in hospital by daily physician review and, post discharge, through study visits and by telephone where possible for children who are lost to follow-up. Morbidity during hospitalisation is assessed through daily clinical assessments and available hospital laboratory tests. Morbidity after discharge is assessed, first, using daily morbidity diaries, in which caregivers record episodes of illness (lethargy interfering with feeding; respiratory distress; diarrhoea; oedema and fever); second, from caregiver recall and review of handheld medical records at each follow-up visit; and, third, from data collected during hospitalisation for children who are readmitted during the follow-up period. Time-to-recovery from malnutrition will be evaluated during hospitalisation; relapse of malnutrition during follow-up will be categorised as moderate acute malnutrition, uncomplicated SAM and complicated SAM, according to WHO definitions. Nutritional outcomes will be expressed both as continuous variables (attained Z-score and change in Z-score between visits), and as categorical variables (moderate wasting, WHZ<–2; severe wasting, WHZ<–3; stunting, HAZ<–2; severe stunting, HAZ<–3; underweight, WAZ <–2; and microcephaly, head circumference-for-age <–2).

Risk factors will be evaluated at baseline, hospital discharge and over the period of follow-up for associations with clinical and nutritional outcomes. In addition to baseline clinical and demographic factors, the following laboratory parameters will be evaluated: haemoglobin, serum albumin, C reactive protein (CRP), CD4 count and HIV viral load (for HIV-positive children). Haemoglobin, CD4 and HIV-viral load will be measured in real time and the results reviewed during follow-up clinics.

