### Observational cohort

The primary comparison will be the clinical and nutritional outcomes of children with HIV-SAM compared with HIV-negative children with SAM. We will review all deaths and adjudicate clinical diagnoses and causes of death to ensure robust and consistent data across sites. We will compare each participant’s clinical management to WHO guidelines to identify any contributory factors in hospital care. Factors associated with outcomes during hospitalisation (eg, mortality, nutritional recovery) will be determined for each group (HIV-SAM and HIV-negative children with SAM) using multivariable analysis (Cox models for time-to-event data, linear models for continuous outcomes). Factors associated with outcomes over 48 weeks post discharge (hospital readmission, morbidity and mortality, relapse, anthropometry, body composition and response to ART) will be determined for each group (HIV-SAM and HIV-negative children with SAM) using multivariable analysis (Cox models for time-to-event data, linear models for continuous outcomes). HIV-positive children with SAM and HIV-negative children with SAM will be included in one model together with the risk factors, and interaction tests will be used to investigate whether associations between risk factors and outcomes differ between the two groups of children. We will evaluate the ability of MUAC at discharge to predict long-term outcomes using receiver-operator-characteristic (ROC) analysis, in the whole cohort and within the subgroups of HIV-SAM and HIV-negative children with SAM. We will then evaluate whether addition of other variables improves the predictive capacity of MUAC (using WHO criteria in those >6 months, and published data for children <6 months^62^) for each group, including body composition, haemoglobin, albumin and CRP, plus CD4%, viral load and timing of ART initiation (HIV-SAM only). We will construct multivariable models and compare them with MUAC alone using the net-reclassification index.

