### Enteropathy substudy

The primary comparison for the enteropathy substudy will be between HIV-positive children with SAM (group A) and HIV-negative children with SAM (group C), stratified by presence or absence of oedema. Control groups (B and D) are well-nourished children with or without HIV, to provide normative data for biomarkers and to evaluate the impact of SAM within each HIV group. Thus, biomarkers among HIV-positive children with SAM will first be compared with HIV-negative children with SAM (to evaluate the impact of HIV) and, second, with well-nourished HIV-positive children (to evaluate the impact of SAM). Biomarkers among HIV-negative children with SAM will be compared with well-nourished HIV-negative children. For each continuous outcome, simple descriptive analysis will be used to compare groups during hospitalisation using t-tests on appropriately transformed data. For any outcome with moderate (p<0.05), evidence of difference between either group a regression model will be constructed including groups A, B, C and D to directly test (using interactions) whether there is a synergistic effect of HIV-SAM versus HIV-negative SAM versus HIV alone versus neither. These models will also be used to explore whether there is any evidence for heterogeneity in effects between oedematous and non-oedematous SAM. Associations between enrolment factors (eg, intestinal permeability and microbial translocation) will be explored using pairwise Spearman correlations and principal components analysis. Mean changes at the follow-up time points in each group will be estimated, and groups compared (as above) using generalised estimating equations. For outcomes that differ across SAM groups over time, multilevel models will be used to explore possible predictors from the other factors measured. Time to nutritional recovery will be compared using Kaplan-Meier and log-rank tests, and Cox models to adjust for baseline differences between groups.

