### Immunology substudy

Integrated profiles of innate immune cell function will be generated for each child using principal components analysis followed by hierarchical clustering.^65 66^ This data -reduction method identifies whether absolute levels of specific markers or relative differences between markers differentiate children into groups. The resulting innate immune profiles will be compared between HIV-SAM, HIV-negative children with SAM and well-nourished groups using univariable tests and multivariable analysis of variance of the principal components.

To address the relationship between immune function and infections, regression analyses will determine whether baseline innate immune profiles (or the individual parameters defining them) are associated with the infectious morbidity or mortality during hospitalisation, using logistic models for binary outcomes and linear models for duration. Key clinical characteristics, including age, sex, oedema and baseline WHZ, will be added to models to investigate their confounding effects. Multivariable stacked regression methods will be used to compare the impact of different factors on severe bacterial infections based on heterogeneity tests.

To determine whether treatment for SAM restores innate immune cell antibacterial function, mixed effects regression models will compare longitudinal changes in individual immune parameters, and the principal components calculated from the weights identified at baseline (which include well-nourished controls). Similarities and differences in longitudinal immune profiles will be compared between groups using non-metric multidimensional scaling.^65 67 68^ This approach will group children according to their composite innate immune function, allowing the duration and variability of immune restoration to be evaluated over the course of nutritional rehabilitation. Binary logistic regression will determine whether innate immune profiles at discharge are associated with morbidity or mortality during follow-up.

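### Time to nutritional recovery is assigned to Kaplan-Meier, log-rank and Cox without treating death as a competing event, so 1-KM would overstate the proportion recovering, most in HIV-SAM

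*Protocol article*

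**What the plan says.** The Analysis section for the enteropathy substudy ends with: "Time to nutritional recovery will be compared using Kaplan-Meier and log-rank tests, and Cox models to adjust for baseline differences between groups". Under Study outcomes and risk factors, the period is set: "Time-to-recovery from malnutrition will be evaluated during hospitalisation".

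The Analysis section for the observational cohort makes HIV-SAM against HIV-negative SAM the primary comparison. It names Cox models for time-to-event outcomes in hospital, with mortality and nutritional recovery as its examples. It names Cox again for the period after discharge: "Factors associated with outcomes over 48 weeks post discharge (hospital readmission, morbidity and mortality, relapse, anthropometry, body composition and response to ART".

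No section mentions competing risks or cumulative incidence, or says how a child who dies before recovering, relapsing or being readmitted is coded.

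The Introduction gives the background on death and recovery by HIV status. Inpatient deaths are almost fourfold higher in HIV-SAM "compared with HIV-negative children with SAM (30.4% vs 8.4%), for reasons that remain unclear". It adds that these children "tend to have delayed nutritional recovery and have a more complicated clinical course than HIV-negative children with SAM".

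**The concern.** Kaplan-Meier for recovery needs a rule for children who die first. The default is to censor them at death, which treats them as still able to recover later. The complement of the curve (1-KM) then estimates the proportion that would recover if nobody died. It is higher than the proportion that does recover, and the excess grows with the death rate.

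Here the competing event is common, and on the article's cited figures it differs 3.6-fold between the two groups being compared. The distortion is therefore unequal and flatters HIV-SAM. Describing outcomes by HIV status is the first primary objective, so a recovery curve that is too high in one group matters even in an exploratory analysis.

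The same reasoning applies to relapse and readmission: a child who has died can no longer have either event. There the article names Cox only, so the risk lies in how the hazard ratio is read and in any curve drawn beside it.

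**Working it through.** **Inputs from the article.** Inpatient deaths 30.4% (HIV-SAM) and 8.4% (HIV-negative SAM), from the Introduction. Cohort planning values of 15% mortality and 40% HIV prevalence, from Sample sizes. Groups of 100 v 100 in the enteropathy substudy.

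**The article's own figures.** 30.4/8.4 = 3.62, consistent with almost fourfold; 30.4 − 8.4 = 22.0 points. For the cohort, 800 × (1 − 0.15 − 0.15) = 560 evaluable and 0.40 × 560 = 224 with HIV-SAM; both reproduce. No power or precision is stated for time to recovery.

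**Assumptions not in the article.** Constant hazards; every child eventually recovers or dies in hospital; a chosen recovery speed.

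**Formulas.** Let r be the recovery hazard and d the proportion who die first.
- Total hazard: r/(1 − d).
- 1-KM with deaths censored: 1 − exp(−rt).
- True cumulative incidence of recovery: (1 − d) × [1 − exp(−rt/(1 − d))], which tends to 1 − d.

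**Step 1: equal recovery hazards, mean 14 days, day 42 (rt = 3).**
- 1-KM, both groups: 1 − exp(−3) = 95.0%.
- True, HIV-SAM: 0.696 × [1 − exp(−3/0.696)] = 0.696 × 0.9866 = 68.7%.
- True, HIV-negative: 0.916 × [1 − exp(−3/0.916)] = 0.916 × 0.9622 = 88.1%.

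The curve is too high by 26.3 points in HIV-SAM and by 6.9 in HIV-negative children. The eventual proportions are 69.6% and 91.6%.

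**Step 2: slower recovery in HIV-SAM, as the Introduction expects.** Take a recovery hazard ratio of 0.7 (assumed), a median of 14 days for the HIV-negative recovery hazard, and day 60. HIV-negative rt = ln 2 × 60/14 = 2.971; HIV-SAM rt = 0.7 × 2.971 = 2.079.

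| | HIV-SAM | HIV-negative | Gap (points) |
|---|---|---|---|
| 1-KM at day 60 | 87.5% | 94.9% | 7.4 |
| True at day 60 | 66.1% | 88.0% | 21.9 |
| True eventually | 69.6% | 91.6% | 22.0 |

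The overstatement in HIV-SAM does not depend on equal hazards.

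**Step 3: range for the eventual gap.**
- If the same fraction f of survivors recovers in each group, the gap is 22.0 × f: 22.0 points at f = 1, 17.6 at 0.8, 11.0 at 0.5.
- Splitting the 15% planning mortality by the 3.62 ratio at 40% HIV prevalence gives 0.15/(0.6 + 0.4 × 3.62) = 7.3% and 3.62 × 7.3% = 26.5%, a gap of 19.2 points at f = 1. The 15% covers the whole study, so the inpatient share would be smaller.

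**Step 4: what the log-rank test sees.** Simulation with 100 v 100, 4,000 runs, two-sided 0.05, median 14 days, deaths censored:

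| Recovery hazard ratio | 1.0 | 0.9 | 0.8 | 0.7 | 0.6 |
|---|---|---|---|---|---|
| Rejection | 5% | 10% | 29% | 62% | 90% |

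At a ratio of 1.0, keeping deaths at risk as never recovered gives 82% rejection, because that test addresses the proportion recovering.

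**The case against.** The strongest reply is that the article never says deaths are censored, and that coding rules of this kind are commonly left to the full protocol or analysis plan. That is correct as to the text: censoring of deaths is the default reading of the named methods, not a stated rule. The point survives because the article fixes the methods themselves. Getting the proportion recovering from them would require a later document to add a competing-risk method.

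Three further objections stand and limit the point.
- Log-rank and Cox with deaths censored validly compare cause-specific recovery rates. The 5% rejection under equal hazards is the correct null rate, not a failure of the test.
- In-hospital mortality is a separate outcome in the observational cohort analysis and all deaths are reviewed. A reader will see the excess deaths, although this does not correct the recovery curve.
- The 30.4% and 8.4% come from a cited source and are not design inputs. The substudy enrols children aged 6–59 months with a nasogastric tube, and its rates may differ.

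Stronger readings that a reader might infer are not supported.
- **That the plan hides a 22-point difference in recovery.** The 22 points are a mortality gap. They become a recovery gap only if all survivors recover in hospital, and complete concealment also needs equal recovery hazards, whereas the Introduction expects delayed recovery in HIV-SAM.
- **That recovery is informatively censored at discharge.** The article does not state this censoring, and following recovery past discharge would change an outcome it confines to the hospital stay.
- **That the immunology models ("using logistic models for binary outcomes and linear models for duration") count early death as a favourable short duration.** This assumes a coding the article does not give.

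**Conclusion.** The point holds in a limited form. Run in their default way, the named methods give a recovery curve that overstates the proportion recovering, and does so unequally by HIV status. On the cited mortality figures and the stated exponential assumptions, the excess at day 42 is about 26 points in HIV-SAM and 7 in HIV-negative children. With a recovery hazard ratio of 0.7 the curve at day 60 shows a gap of about 7 points where the true gap is about 22. These sizes are illustrations: they shrink if fewer survivors recover in hospital or if study mortality is below the cited rates.

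The error is confined to reading 1-KM, or the hazard ratio, as the proportion who recover. The cause-specific tests are sound and the mortality comparison is unaffected. For relapse and readmission the direction is the same, but no size is given here, because inpatient death rates do not describe the period after discharge.

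**What to change.** For nutritional recovery, replace the Kaplan-Meier curve by Aalen-Johansen cumulative incidence with death as a competing event, and compare groups with Gray's test. Do the same for relapse and readmission. Label log-rank and Cox results for these outcomes as cause-specific, and report them beside the cause-specific hazard ratio for death, so that slower recovery and more deaths can be told apart. Keep Kaplan-Meier and Cox for all-cause mortality.

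The cost is a few sentences of analysis text and a little extra programming. Daily inpatient review and the follow-up visits already collect the data needed, and no sample size changes.

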### Microbiota and metabolomics substudy

The primary comparison will be between HIV-negative children with oedematous and non-oedematous SAM, with a separate comparison between HIV-positive children with SAM and HIV-negative children with SAM. Analyses will examine (i) differences in metagenomic/metabolomic variables between groups at each time point; (ii) differences in metagenomic/metabolomic variables within groups over time; (iii) correlations between metagenomic and metabolomic variables and (iv) correlations between metagenomic/metabolomic variables and clinical outcomes. A systematic analysis will be undertaken to reduce high-dimensional data, integrate the multi-omics data sets and minimise false discovery.

Compositional metagenomic data will be compared between groups for indices of alpha and beta diversity. Principal coordinate analysis and partial least-squares discriminant analysis will be performed on metabolomics data to identify overall differences between groups. High-dimensional data sets will be reduced using random forest models to identify taxa, microbial gene families and metabolites that most strongly contribute to differences between groups, corrected by Benjamani-Hochburg false discovery rate detection. Targeted analysis by qRT-PCR will validate differential abundance or expression of candidate microbial genes. Longitudinal comparisons will be performed within and between groups using multilevel simultaneous component analysis. Orthogonal projections to latent structures models will integrate metabolomic and metagenomic data while linear regression, canonical correlation and hierarchal clustering analysis will measure correlations between -omics data sets. Finally, ROC analysis will identify the ability of different analytes to predict long-term nutritional and clinical outcomes.

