## Study design

HOPE-SAM is a longitudinal observational cohort study, enrolling between 600–800 children aged 0–59 months admitted with complicated SAM to the tertiary paediatric wards at two sites in Zimbabwe (Parirenyatwa Hospital and Harare Children’s Hospital) and one in Zambia (University Teaching Hospital, Lusaka). Both HIV-positive and HIV-negative children will be enrolled. Throughout this paper, ‘SAM’ refers to all children, regardless of HIV status; where analyses specifically compare children by HIV status, groups are identified as HIV-positive children with SAM (HIV-SAM) and HIV-negative children with SAM. All participants with SAM are followed for 48 weeks post discharge, with longitudinal data collection and blood sampling. The study contains four nested substudies as shown in figure 1. A subgroup of children will be recruited to the enteropathy substudy for which they will have the same follow-up procedures but more intensive biological specimen collection including stool (all time points), urine after lactulose-mannitol (LM) challenge as an assessment of intestinal permeability and nasogastric aspirate (baseline only); these children are also included in microbiota and metabolomics substudies. Children with SAM for whom blood samples are available are included in the immunology substudy, for which circulating inflammatory mediators will be assayed; functional cellular immunology assays will be conducted for all children in the immunology substudy with sufficient sample volume (>2 mL) recruited after June 2017. A group of healthy children recruited from the same hospitals and communities, who are well-nourished and matched to children in the enteropathy substudy by age and HIV status, will have data and specimens collected to provide normative data for the laboratory substudies; these well-nourished controls will not be followed longitudinally.

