### Eligibility for enteropathy substudy

Children with SAM aged 6–59 months with a nasogastric tube in place (or due to be placed) are categorised into four groups (HIV-positive oedematous (group A -I); HIV-positive non-oedematous (group A-II); HIV-negative oedematous (group C-I) and HIV-negative non-oedematous (group C-II)) as shown in table 1. Children meeting eligibility criteria will be enrolled throughout the study recruitment period until sufficient specimens have been collected from the groups shown in table 1. Children in the enteropathy substudy are stratified into age bands (6–11 months, 12–23 months and 24–59 months) to enable age-matching of well-nourished controls. Children with underlying chronic gastrointestinal disease or a known malignancy are ineligible.

**Table 1 T1:** Enteropathy substudy groups

Children aged 6–59 months	SAM*		Well-nourished controls WHZ>–1
	Oedematous†	Non-oedematous	
HIV-positive (HIV PCR+ if <18 months; HIV antibody+ if >18 months)	n=50 (group A-I)	n=50 (group A-II)	n=100 (group B)
HIV-negative (HIV PCR– if<18 months; HIV antibody – if>18 months)	n=50 (group C-I)	n=50 (group C-II)	n=100 (group D)

Note that children below 6 months of age are excluded from the enteropathy substudy to avoid interrupting exclusive breast feeding during the lactulose-mannitol test.

*SAM defined according to WHO criteria.

†Presence of bilateral pitting pedal oedema.

SAM, severe acute malnutrition; WHZ, weight-for-height Z-score.

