### Eligibility for microbiota and metabolomics substudies

Children enrolled into the enteropathy substudy are also included in the microbiota and metabolomics substudies since these substudies use the stool, urine and plasma samples collected for enteropathy analyses.

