### Microbiota substudy

Normal assembly of the gut microbiota in early life is critical for many aspects of physiological, neurological and immune development.^38^ Recent evidence suggests that an immature or pathogenic microbiota plays a causative role in the pathogenesis of SAM.^25^ For example, a number of microbial taxa have been identified, including *Faecalibacterium prausnitzii*, which discriminate and predict gut microbiota maturity and child growth.^28^ Other pathogenic microorganisms, including IgA-targeted *Enterobacteriaceae*, are associated with impaired growth and may contribute to SAM.^39^ Nutritional rehabilitation with RUTF induces temporary recovery of a disturbed microbiota; however, the microbiota appears to revert back to an immature diseased state following nutritional recovery.^29^ HIV infection is also associated with a disturbed gut microbiota,^40^ which may further compound enteropathy phenotypes. Furthermore, there is some evidence that differences exist in malnutrition enteropathy between oedematous and non-oedematous SAM^41^; however, few studies have investigated differences in the gut microbiota between the two forms of the disease.

We hypothesise that (i) a unique gut microbial signature exists in HIV-SAM, compared with HIV-negative children with SAM, that is independently associated with morbidity, mortality, nutritional recovery and degree of enteropathy during hospitalisation; (ii) a unique gut microbial signature exists in oedematous compared with non-oedematous SAM; (iii) specific microorganisms or gut microbial diversity indices are independently associated with morbidity, mortality, nutritional recovery and degree of enteropathy during hospitalisation; and (iv) the gut microbiota is partially restored to a healthy state with nutritional rehabilitation but reverts to a dysbiotic state during follow-up, which predicts morbidity, mortality and relapse of SAM.

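### The microbiota and metabolomics group contrasts are specified without age, and nothing stated balances age between the SAM groups, so an age gap could be read as a signature of oedema or HIV

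*Protocol article*

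**What the plan says.** All references are to the protocol article.

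- **Contrast.** Under Analysis, Microbiota and metabolomics substudy: "The primary comparison will be between HIV-negative children with oedematous and non-oedematous SAM". HIV-positive v HIV-negative children with SAM is a separate comparison.
- **Claim under test.** The Microbiota substudy section hypothesises that "a unique gut microbial signature exists in oedematous compared with non-oedematous SAM", and makes a parallel claim for HIV-SAM. The Metabolomics substudy section makes a similar claim for oedematous SAM.
- **Methods.** The same Analysis section names alpha and beta diversity by group, principal coordinate and PLS discriminant analysis, and "random forest models to identify taxa, microbial gene families and metabolites that most strongly contribute to differences between groups", with false discovery rate control. No covariate is named for the group contrast. Linear regression appears there only for relating the -omics data sets to one another.
- **Participants.** "Children enrolled into the enteropathy substudy are also included in the microbiota and metabolomics substudies". They are aged 6–59 months, and Table 1 plans 50 children in each of the four oedema-by-HIV groups.
- **Age in the design.** Substudy children are "stratified into age bands (6–11 months, 12–23 months and 24–59 months) to enable age-matching of well-nourished controls". Study design says that the controls are "matched to children in the enteropathy substudy by age and HIV status". Under Sample sizes, the only stratification target within the SAM groups is oedema, and only if feasible.
- **Age and the microbiota.** The Microbiota substudy section refers to normal assembly in early life and to taxa "which discriminate and predict gut microbiota maturity and child growth".

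**The concern.** A gut microbiota that matures with age, sampled across an age range of more than four years, will differ between any two groups that differ in age. Oedema and HIV status are observed, not assigned, so there is no reason to expect equal ages. The matching brings well-nourished controls into line with cases; it does not align oedematous with non-oedematous children, or HIV-positive with HIV-negative children with SAM.

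A method that sees only group labels cannot separate an effect of oedema from an effect of age. Taxa that track maturity could then be put forward as a distinctive phenotype of oedematous SAM or HIV-SAM, and the study hopes to use its findings to guide new interventions. False discovery rate control does not help: it limits chance findings, whereas an age-driven difference between the groups is real but has the wrong cause.

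**Working it through.** **1. The plan's own figure.** Under Sample sizes, this substudy is said to need 95–126 subjects by analysis of covariance (alpha 0.05, 80% power, correlation 0.1 or 0.7). The effect is a 50% difference in metabolites, with no SD. Reading that as 0.5 SD (an assumption), the unadjusted number per group is 2 × (1.960 + 0.842)² / 0.5² = 62.8.

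- Correlation 0.1: 62.8 × (1 − 0.01) = 62.2, so 63 per group and 126 in total. This matches the upper figure.
- Correlation 0.7: 62.8 × (1 − 0.49) = 32.0, so 33 per group and 66 in total, not 95.

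Without an SD the range cannot be called wrong, and nothing below depends on it. What matters is that the covariate is not identified and the Analysis section names no analysis of covariance.

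**2. Is age balanced or adjusted anywhere for these contrasts?**

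| Place | Use of age | Links oedematous to non-oedematous, or HIV-positive to HIV-negative SAM? |
|---|---|---|
| Eligibility for enteropathy substudy | Bands, for control matching | No |
| Study design; Well-nourished controls | Controls matched to cases | No |
| Sample sizes, enteropathy | Not mentioned; stratified by oedema | No |
| Analysis, microbiota and metabolomics | No covariate named | No |

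**3. What an age gap would do to one feature.** Inputs from the document: 50 v 50 (Table 1). Assumed inputs, because the document gives none: age gap g in SD units, within-group correlation r between feature and age, and true oedema effect zero.

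- False standardised difference = r × g.
- Noncentrality = r × g × √(50/2).
- For r = 0.5, g = 0.5: difference 0.25 SD, noncentrality 0.25 × 5 = 1.25, and two-sided rejection at nominal 5% is 23.6% (noncentral t, 98 df). The normal approximation gives 24.0%.

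Unadjusted rates come from the noncentral t. Adjusted rates come from simulating a linear model with group and age, 4,000 runs per cell (simulation error about √(0.05 × 0.95/4000) = 0.3 percentage points).

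| Age gap (SD) | Unadjusted, r = 0.3 | r = 0.5 | r = 0.7 | Age-adjusted, over the three r |
|---|---|---|---|---|
| 0 | 5.0% | 5.0% | 5.0% | 4.6–4.9% |
| 0.2 | 6.0% | 7.9% | 10.7% | 4.6–5.4% |
| 0.3 | 7.3% | 11.5% | 18.0% | 4.7–5.0% |
| 0.5 | 11.5% | 23.6% | 41.0% | 4.5–5.1% |
| 0.8 | 22.1% | 50.8% | 79.2% | 4.7–4.9% |

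**4. HIV contrast.** With 100 v 100, r = 0.5 and g = 0.5, the noncentrality is 0.25 × √50 = 1.77 and rejection is about 42% (normal approximation). A larger sample makes the bias easier to detect as a difference, not smaller.

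**5. If ages happen to be balanced.** There is no bias. Adjustment would still remove r² of the residual variance: 25% at r = 0.5 and 49% at r = 0.7.

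**The case against.** The strongest objection is that a condensed article commonly leaves covariate lists to the full protocol, which the article says is online and which is not shown here. The article never says that these comparisons will be unadjusted, its sample size rests on analysis of covariance, and it declares all analyses exploratory. This carries weight and keeps the severity down. It does not dispose of the point. The article sets out the methods for this contrast in detail and describes adjustment elsewhere: age- and sex-adjusted Z-scores for body composition, and Cox models adjusting for baseline differences in the enteropathy substudy. The analysis of covariance names no covariate, and exploratory reading of p values does not remove confounding.

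Several stronger readings are tempting but unsupported:

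- **That the groups do differ in age.** The document shows only that no balancing mechanism is stated.
- **That the percentages above are the plan's error rates.** They describe one feature at nominal 5% under assumed gaps and correlations; the plan uses multivariate methods and false discovery rate control.
- **That random forest will rank age-related features highest.** Ranking depends also on true oedema effects, which the calculation sets to zero.
- **That the immunology substudy shows age adjustment for the same kind of analysis.** Its models with age, sex, WHZ and oedema relate immune profiles to infection outcomes. Its own group comparison names no age term either.
- **That maturation is documented for metabolites.** The article describes it for the microbiota only.

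**Conclusion.** The point holds as a gap in the stated analysis. Followed as written, the oedema and HIV contrasts in this substudy use group-only methods in groups with no stated age balance, while the article itself ties taxa to microbiota maturity. An age gap could then be attributed to oedema or HIV.

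The size is unknown and could be nil. Over the assumed non-zero gaps of 0.2 to 0.8 SD and correlations of 0.3 to 0.7, the single-feature false-positive rate runs from 6% to 79% unadjusted and stays near 5% adjusted. For metabolomics the same confounding is plausible but not described. This is a cheap improvement of low to moderate severity, subject to what the full protocol or analysis plan may already contain.

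**What to change.** - Report the age distribution by oedema group and by HIV group.
- Include age, continuous or in the existing three bands, as a covariate in the models for diversity indices and single features.
- In the beta-diversity tests, enter age as a covariate or permute within age band.
- Before calling a feature selected by random forest or PLS discriminant analysis a signature of oedema or HIV, confirm it in an age-adjusted model. Residualising features on age before classification is one alternative, but it can remove real signal where age and oedema are associated, so it need not be required.

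The cost is one or two degrees of freedom, modest extra computation and a few sentences of text. The substudy children are already assigned to age bands, so no new data are needed. If the full protocol or analysis plan already specifies age adjustment, a cross-reference is enough.
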